**10.2 Informed Consent**

The investigator should fully inform the participant of all pertinent aspects of the study, including the written information. All written and/or oral information about the study will be provided as nontechnical as practical and understood by the participants. The participants should be given ample time and opportunity to inquire about details of the study and to decide whether or not to participate in the study.

Written informed consent will be obtained from each participant before any study-specific procedures or assessments are done and after the aims, methods, anticipated benefits, and potential hazards are explained. The participant’s willingness to participate in the study will be documented in a consent form, which will be signed and personally dated by the participant and by the person who conducted the informed consent discussion. The investigator will keep the original consent forms, and copies will be given to the participants. It will also be explained to the participants that the participant is free to refuse entry into the study and free to withdraw from the study at any time without prejudice to future treatment. As the blood and urine sampling for clinical laboratory tests and analyzes is an integral part of this study, the main Informed Consent Form covers these analyzes.

The investigator must identify vulnerable participants, that is, participants whose willingness to participate in this study might be unduly influenced by the expectation, regardless of whether it is justified, of benefits associated with participation, or of a retaliatory response from senior members of a hierarchy in case of refusal to participate. Participants thus identified must be excluded from participation in the study.

The participants must be informed that persons authorized by the acupuncturist, the clinical research assistant, the statistician, and the principal investigator may view their medical records. The confidentiality of the participants will in all cases be respected.

The consent procedures described above will only be implemented if allowed by law and regulations and will only be initiated after approval by the relevant ethics committees.

**10.3 Personal Data Protection**

The investigator must ensure that the privacy of the participants, including their identity and all personal medical information, will be maintained at all times. In CRFs and other documents submitted to the principal investigator, participants will be identified not by their names, but by an identification code (i.e., identification number).

Personal medical information may be reviewed for the purpose of participants safety and/or verifying data in the source and transcribed onto the CRFs. This review may be conducted by the investigators. Personal medical information will always be treated as confidential.

The investigators are responsible for ensuring the privacy, health, and welfare of the participants during and after the study and must ensure that trained personnel are immediately available in the event of a medical emergency. The investigators must be familiar with the background to, and requirements of, the study and with the contents of the treatments and medications as described in the interventions.

**10.4 Research Ethics Committees**

Before this study starts, the protocol will be submitted to the Research Ethical Committee for review. As required, the study will not start before the Research Ethical Committee to give written approval or a favorable opinion.

**11. DATA HANDING AND RECORD KEEPING**

**11.1 Data Collection**

**11.1.1Electronic** **Case Report Forms (eCRFs)**

CRFs will be used to collect all the data related to the study. The baseline characteristics of patients will be recorded by our investigator during the baseline period in CRFs, and the data manager will review all data. Upon the completion of the treatment and follow-up periods, all patients’ data will be completed and recorded on the original CRFs, following which the data manager will check data sets to ensure accuracy. If any inconsistencies are noted, corrections will be made according to, and marked on, the original CRFs.

The eCRFs use third party database (Beijing LNKMED Tech Company Limited) to capture data via an online system on a computer. When the investigator enters data in the eCRF (ideally during the visit or as soon as possible [<3 days] thereafter), the data will be recorded electronically in the database, and all entries and modifications to the data will be logged in an audit trail. Access to the system will only be granted after appropriate and documented training. Written instructions for using the system will be provided along with the training.

Electronic signatures will be used where signatures are required on pages and/or visits. Automated data entry checks will be implemented where appropriate; other data will be reviewed and evaluated for accuracy by the principal investigator. All entries, corrections, and changes must be made by the investigator.

**11.1.2 Patient Binders**

A Patient Binder will be provided for each patient. The Patient Binder contains different types of source documents, organized by visit and type. A ballpoint pen with waterproof ink must be used to enter information in the Patient Binder. The Patient Binder also contains Serious Adverse Event Fallback Forms. These forms must be used when the eCRF cannot be accessed.

**11.2 Database Management and Quality Control**

Quality control will be applied to ensure that all data are reliable and have been processed correctly, both during and after the trial. After the data is entered in the eCRFs, the principal investigator’s designee must perform source data verification check systematically for accuracy, consistency, completeness, and reliability, including a comparison of the data in eCRFs with source documents. Data should only be included in the final analysis when checks have been satisfactorily completed. If data does not pass validation rules, data queries will be addressed to the investigator to request clarification or correction. The investigator is obliged to respond by confirming or modifying the data questioned.

**11.3 Retention of Study Documents**

**Principal Investigator Responsibilities**

The principal investigator will have final responsibility for the processing and quality control of the data. Data management oversight will be carried out as described in the standard operating procedures (SOPs) for clinical studies. These SOPs will be reviewed by the principal investigator before the start of data management activities. The original CRFs will be archived by the principal investigator.

**Investigator Responsibilities**

The investigator must maintain all written and electronic records, accounts, notes, reports, and data related to the study and any additional records required to be maintained, including, but not limited to, the following: full case histories, signed informed consent forms, patient identification lists, CRFs for each patient on a per-visit basis, data results from other sources (e.g., TMD diary data), safety reports, reports of receipt, use. The investigator will retain all records related to the study until principal investigator sends written notification that records may be destroyed.

All paper research-related documents will be maintained in a closed file cabinet. All research materials, including hard copies and digital data, will be kept on file for at least five years following publication.

Before the study has been completed, the investigator can read and entry to the eCRF. After the study has been completed, all user access to the eCRF will be revoked. And the eCRF cannot be modified again.

At the end of the study, Beijing LNKMED Tech Company Limited will be provided with all data related to the study (including CRF data, queries, and the audit trail) using a secure electronic medium. When confirmation of receipt of the data has been received from Beijing LNKMED Tech Company Limited all user access to the CRF will be revoked. If, for some reason, the data are not readable for the full retention period, the investigator may request that the data be re-sent.

**12. STATISTICAL METHOLOGY**

A general description of the statistical methods is outlined below. A more detailed Statistical Analysis Plan will be provided in a separate document that will be finalized prior to database lock.

**12.1 Analysis Sets**

**12.1.1 Intention-to-Treat Analysis Set**

The Intention-to-Treat (ITT) analysis set will include all randomized participants. In this population, treatment will be assigned based on the treatment to which participants are randomized, regardless of which treatment they actually received.

**12.1.2 Per-Protocol (PP) Analysis Set**

The per-protocol (PP) analysis set was a subset of the ITT analysis set, including only participants who completed the study without any violations of the inclusion/exclusion criteria, or any deviations or omissions in the study treatment plan.

**12.1.3 Safety Analysis Set**

The safety analysis set will include all participants who receive at least one treatment. In this population, treatment will be assigned based upon the treatment participants actually receive, regardless of the treatment to which they are randomized.

**12.2 Sample Size and Power**

Based on our pilot study, the reduced pain intensity of TMD patients after 4 week treatment was 3.4±0.3 in the acupuncture group and 2.9±0.7 in the sham acupuncture group. A sample size of 50 patients gives at least 90% power for the study to succeed at an alpha level of 0.05. Assuming a 10% loss rate of follow-up, 30 patients per treatment group were planned for this study.

**12.3 Descriptive Statistics**

All summary statistics will be computed and displayed by treatment group. In general, summary statistics (count [n], mean, least-squares mean [LSM], standard deviation [SD], standard error [SE], median, lower and upper quartiles, minimum and maximum values) will be presented for continuous variables and counts and, if relevant, percentages will be presented for categorical variables. Graphical data displays may also be used as appropriate.

**12.4** **Participants Disposition**

Data from participants screened, participants screened but not randomized and reason not randomized, participants who are randomized (i.e., in the ITT set), participants randomized but not treated, participants in the safety and other analysis sets, participants who complete the study, and participants who withdraw from the study will be summarized using descriptive statistics. Data from participants who withdraw from the study will also be summarized by reason for withdrawal using descriptive statistics.

**12.5** **Demographics and Baseline Characteristics**

Participant demographics and baseline characteristics (sex, age, BMI, current employment status, education, marital status, and annual income, facial pain, DC/TMD examination findings) and baseline efficacy variables, will be summarized by treatment group using descriptive statistics.

**12.6 Efficacy analyzes**

**12.6.1 General Efficacy Analysis Methodology**

The ITT set (see **section 12.1.1**) will be used for all efficacy analyzes. Summaries will be presented by treatment group.

**12.6.2 Primary Analysis of the Primary Outcome**

The linear regression model will be applied for the primary outcome (change from baseline in mean weekly pain intensity at week 4). The model will include treatment as fixed effect; Sex, age, weekly pain intensity at baseline, TMD-specific medication as covariates. The LSM change from baseline with standard error (SE) was presented for each treatment group, and the LSM with 95% confidence intervals (95% CIs) for the treatment differences, and associated p-values will be provided.

### 12.6.3 Analysis of the Secondary Outcomes

For the proportion of responders of ≥30% and ≥50% reduction in weekly pain intensity, a logistic regression model was implemented adjusted for sex, age, weekly pain intensity at baseline, TMD-specific medication. Mean percentage with SE, and odds ratios with 95% CIs were presented for these efficacy outcomes by 4 weeks.

The analysis of continuous secondary outcomes were performed similarly to the primary efficacy outcome. A linear regression method, which is similar to the primary analysis setup, will be used for the analysis of the mean change from baseline in jaw opening and movement, GCPS, JFLS-20, DASS-21, PSQI, PPT, and sEMG at week 4. The LSM change from baseline with SE was presented for each treatment group, and the LSM with 95% CIs for the treatment differences, and associated p-values will be provided.

### 12.6.4 Analysis of the Exploratory Outcomes

The analysis of change from baseline in weekly pain intensity at week 8 were performed similarly to the primary efficacy outcome, and the proportion of responders of ≥30% and ≥50% reduction in weekly pain intensity, the jaw opening and movement, GCPS, JFLS-20, DASS-21, PSQI at week 8 were performed similarly to the secondary efficacy outcome.

**12.7 Safety analyzes**

The safety population will be used for all safety analyzes. Summaries will be presented by treatment group unless specified otherwise.

### 12.7.1 Acupuncture Administration

Number (%) of patient receiving each session of acupuncture will be summarized using descriptive statistics by treatment group.

### 12.7.2 Adverse Events

The incidence of AE and severity of the AE will be summarized using descriptive statistics. Each patient will be counted only once by using the AEs with the highest severity within each category. Treatment-related AE summaries will include AEs related to acupuncture.

Listings for SAEs, AEs will be presented. All information pertaining to AEs noted during the study will be listed by subject, detailing verbatim given by the investigator, date of onset, date of resolution, severity, and relationship to treatment. The onset of AEs will also be shown relative (in number of days) to the first day of treatment. In addition, AE descriptions, and AE by patient number and treatment group will be presented.

### 12.7.3 Clinical Laboratory Tests/ Vital Signs/ Weight

The incidence of potentially clinically significant abnormal results will be summarized using descriptive statistics. Listings of patients who have potentially clinically significant abnormal data will be presented.

**13. MONITORING PROCEDURES**

**13.1 Procedures for Monitoring Participant Compliance**

The investigator will be responsible for monitoring participant compliance (acupuncture sessions). If the principal investigator determines that the participant is not in compliance with the study protocol, the principal investigator must inform the Research Ethical Committee and they must review, discuss, and document the implications of the deviation.

**13.2 Study Monitoring**

To ensure compliance with GCP guidelines, the study monitor is responsible for ensuring that participants have signed the informed consent form and the study is conducted according to applicable SOPs, the protocol, and other written instructions and regulatory guidelines.

The main responsibilities of the study monitor are to visit the investigator before, during, and after the study to ensure adherence to the protocol, that all data are correctly and completely recorded and reported, and that informed consent is obtained and recorded for all participants before they participate in the study and when changes to the consent form are warranted, in accordance with Research Ethical Committee approvals.

The study monitor will be permitted to check and verify the various records (CRFs and other pertinent source data records, including source documentation) relating to the study to verify adherence to the protocol and to ensure the completeness, consistency, and accuracy of the data being recorded.

The investigator must agree to cooperate with the study monitor to resolve any problems, errors, or possible misunderstandings concerning the findings detected in the course of these monitoring visits and/or provided in follow-up written communication.

1. **STUDY DISCONTINUATION**

The investigators may choose to discontinue study treatment, if they think the continuation would be detrimental to the participants’ well-being. Whenever possible, the participants should be re-challenged with study treatment if their conditions were considered appropriate by the investigator. Participants also have the right to discontinue study treatment at any time for any reason, without prejudice to further treatment. Such participants will always be asked about the primary reason for their decision to discontinue study treatment and the presence of adverse events if any. If the discontinuation was due to adverse events, refer to the **section 9.** It should be evaluated if the discontinuation can be made temporarily, and permanent discontinuation should be the last choice.

It is essential to collect as much data as possible for all participants throughout the study, especially all potential endpoint events. Discontinuation of study treatment does not mean discontinuation of follow-up or termination of study participation. Participants who have discontinued performance of study treatment are expected to, and should be encouraged to, remain in follow-up until the end of study.

**16. PUBLICATIONS**

Principal investigator has ownership of all data and results collected during this trial. All decisions regarding the use of data and results for public presentations and publications must be approved by principal investigator.

All presentations and publications of the results will be based on clean, checked, and validated data in order to ensure the accuracy of the results. The results of this trial will be published irrespective of whether the results are regarded positive or negative.

**17. FUNDING**

This study was funded by Beijing Traditional Chinese Medicine Science and Technology Project (JJ2018-53).

**18. SUMMARY OF CHANGES TO PROTOCOL**

**Protocol Changes Version 1.0 (Oct. 17, 2018) to 1.1 (Mar. 5, 2019)**

- Exclusion criteria

Patients received concomitant therapy for managing facial pain is added.

- Study design

The screening period is added.

- Secondary Outcomes

30% and 50% reduction in mean weekly pain intensity are added.

The jaw opening and movement is added.

- Exploratory Outcomes

Secondary outcomes during weeks 5-8 are retitled as exploratory outcomes.

**APPENDIX**

**APPENDIX A. TMD Diary**

| **Study Period**  （Please draw √ inside the present period brackets） | **Baseline period**  (-1-0 Week)  ( ) | **Treatment period**  (1-4 Week)  ( ) | **Follow-up period**  (5-8 Week)  ( ) |
| --- | --- | --- | --- |

**Subject Diary Card - TMD diary**

**Random Number：_____________________________**

**Time of This Visit：___________________(yy/mm/dd)**

**[Filling Explanation]**

Your TMD diary is used to record all the symptoms associated with your TMD pain. Please try your best to answer these questions on the day of TMD pain or the day after TMD pain. You need to record all symptoms you observe. Please try your best to ensure accuracy and completeness.

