**7.3 Treatment Period**

Participants will receive acupuncture or sham acupuncture for twelve sessions (3 sessions per week, ideally every other weekday for 4 weeks) during the treatment period.

At the visits during the treatment period, the investigator will review medical history, record the change from baseline in mean weekly pain intensity at week 4 and record concomitant medications, specified concomitant therapies and AEs. Daily TMD diaries will be collected and compliance with diaries will be assessed. When participant has left, assess participant compliance with study therapy usage.

Additional assessments of the GCPS, JFLS-20, DASS-21, PSQI, PPT, and sEMG will also be accessed during treatment period.

Vital signs and weight will be recorded every week during the treatment period. The AEs will be monitored and recorded during the treatment period.

The patient satisfaction will be measured by Participants’ satisfaction scale at the end of treatment period. Patients will rate how they describe the satisfaction since beginning the treatment in this study on a 5-point scale where 1=extremely dissatisfied; 2=dissatisfied; 3=moderately satisfied; 4=satisfied; 5=extremely satisfied. Participants who achieve score 4 or score 5 are considered as responoders. Participants compliance will be checked every week during the treatment period and at least 50% entries with the TMD diary should be attained.

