**8.2.2 TMD Diary**

The patient will be instructed to complete a TMD diary daily from baseline until completion. Eligible patients will receive comprehensive training from investigators on the use of the TMD diary. Investigators will also instruct patients on the requirement for timely and daily completion of the TMD diary.

The day of TMD diary distribution will start the 7-day TMD diary baseline period during which the patient will record daily information regarding pain severity, and intake of pain acute medication. Any patient found to be ineligible for the study during the baseline period or prior to randomization will not be randomized. On each day during the study until the completion/withdrawal, the patient will be asked to record diary data for the previous 24-hour period. For each day, the patient should record if they experienced any pains. Patients will also record any medications (name of drug, number of tablets/capsules, and the dose in milligrams per tablet/capsule) taken on each day. At least 85% compliance of TMD diary is needed during the baseline period and 50% during the treatment and follow-up periods. And the compliance will be assessed every four weeks.

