**Your charge doctor:**

**Tel of your charge doctor：**

**Explanation 1:** Please record a Pain diary **at 19:00** every day and recall your TMD pain from 19:00 yesterday to now **without blank**. If you have a TMD pain, please truthfully record it in the diary, and be sure to record all the details. And remember to **bring back** this TMD diary on each subsequent visit. The following are the problems you may encounter when filling. If you have any questions during the filling process, please contact your doctor in charge.

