## 6.4 Diary Compliance

At least 85% compliance of TMD diary is needed during the baseline period and 50% during the treatment and follow-up periods. And the compliance will be assessed every four weeks.

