## 8.2 Primary Efficacy Variable and Analysis

For the purpose of this study, the change of pain intensity will be defined as the reduced score of weekly pain intensity (reported on a 0-10 VAS) from baseline to the last week of treatment period.

The primary statistical analysis to evaluate the primary hypothesis will use all data from the ITT analytical sample in a linear regression model. Mixed models will be used to analyze the treatment effect at Week 4.

The weekly pain intensity was calculated if a participant completed at least 4 of the 7 daily reports of pain intensity. For patients with missing days and fewer than 4 days of TMD diary data for 1 week, the weekly pain intensity was considered missing before the multiple imputation procedure. The statistics were based on 10 sets of imputed data, where the mean is the average of the means from the 10 data sets and the standard error (SE) of the mean is adjusted based on the imputation variance estimates.

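### The TMD diary card gives two conflicting completion instructions, and if pain-free days are left blank the SAP's weekly mean could overstate week-4 pain

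*Combined protocol and SAP*

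**What the plan says.** **Diary card (Protocol Appendix A).** The Filling Explanation reads "Please try your best to answer these questions on the day of TMD pain or the day after TMD pain". Explanation 1 asks for an entry at 19:00 "every day and recall your TMD pain from 19:00 yesterday to now", and adds "without blank". Explanation 2 anchors the VAS at 0 for no pain. The table has rows for pain start and end times, a 0–10 score, acute medication and adverse events. It has no tick box for a day without pain.

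**Protocol 8.2.2.** "The patient will be instructed to complete a TMD diary daily from baseline until completion". It also says "For each day, the patient should record if they experienced any pains", and provides for investigators to train patients on the diary.

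**SAP 8.2.** The weekly value is calculated when at least 4 of the 7 daily reports exist. Otherwise: "For patients with missing days and fewer than 4 days of TMD diary data for 1 week, the weekly pain intensity was considered missing", and multiple imputation follows (10 data sets). The SAP does not define a blank day. SAP 8.1 and 8.2.1 plan one sensitivity analysis, on the per-protocol set.

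**Diary compliance.** Protocol 8.2.2 and SAP 6.4 set 85% at baseline and 50% during treatment and follow-up. On timing, SAP 6.4 says "And the compliance will be assessed every four weeks", as does Protocol 8.2.2. Protocol 7.3 says "Participants compliance will be checked every week during the treatment period", also with a 50% requirement.

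**The concern.** A patient with no pain today can follow the Filling Explanation and leave the day empty, or follow Explanation 1 and write 0. The two choices give different endpoint values, and the data set will not show whether a blank means no pain or a forgotten entry.

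The resulting error depends on the outcome. At a given pain-day level, the more pain-free days a patient has, the more the weekly mean is overstated. Patients with the most pain-free days may fall below 4 entries and go to imputation. The same weekly values feed the ≥30% and ≥50% responder endpoints. The per-protocol analysis does not test this, because it changes which patients are analysed and not how a blank day is read.

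**Working it through.** **1. The planned difference, for scale.** SAP 3.2 gives reductions of 3.4±0.3 and 2.9±0.7.
- Difference: 3.4 − 2.9 = 0.5. Root-mean-square SD: √((0.3² + 0.7²)/2) = 0.5385.
- Two-sided 5%, 90% power: n per arm = 2 × 0.29 × (1.960 + 1.282)² / 0.5² = 24.4, so 25 per arm and 50 in total. Normal-approximation power at 25 per arm is 90.7%.
- 10% loss: 50/0.9 = 55.6, so 56; the planned 60 covers it.

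The stated sample size reproduces and is not in dispute.

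**2. Error for one patient.** Assume a constant score L on k pain days, 0 on the other 7 − k days, and every pain-free day left blank. Blank days are taken to drop out of the mean, which SAP 8.2 implies without stating.
- True weekly mean = L × k/7.
- Analysed mean = L if k ≥ 4; missing and imputed if k ≤ 3.
- Overstatement for k ≥ 4 = L × (7 − k)/7.

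| Pain days k | L = 2 | L = 3 | L = 5 |
|---|---|---|---|
| 6 | 0.29 | 0.43 | 0.71 |
| 5 | 0.57 | 0.86 | 1.43 |
| 4 | 0.86 | 1.29 | 2.14 |
| 0–3 | imputed | imputed | imputed |

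The range is 0.29 to 2.14 points. If pain-free days are entered as 0, the overstatement is 0. For k ≤ 3 at L = 3, the true mean lies between 0 and 1.29 but is replaced by imputed values.

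**3. Responder status.** Assume a baseline of 5.0, the average intensity quoted in Protocol 1.1.1. With week-4 pain of 3 on four days, the true mean is 12/7 = 1.71, a reduction of 1 − 1.71/5 = 66%. The analysed mean is 3.0, a reduction of 40%. A ≥50% responder is counted as a non-responder.

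**4. Between arms.** Analysed benefit minus true benefit equals the mean error in the sham arm minus the mean error in the acupuncture arm.
- Same L and same k in both arms: the errors cancel.
- L = 2 in both arms, 4 pain days with acupuncture and 6 with sham: true difference 2 × (6 − 4)/7 = 0.57, analysed difference 0. This is attenuation.
- k = 4 in both arms, L = 2 with acupuncture and 3 with sham: true difference 1.71 − 1.14 = 0.57, analysed difference 1.0. This is inflation.

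Attenuation is expected when the better arm gains mainly pain-free days, but it is not guaranteed. For orientation only: if the observed difference shrank from 0.5 to 0.4 or 0.3, power at 25 per arm would fall from 90.7% to 74.7% or 50.4%. The documents give no basis for choosing among these values.

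**5. Compliance checks.**
- Baseline: 0.85 × 7 = 5.95, so 6 of 7 days; at most one blank.
- Treatment, assessed every four weeks: 0.50 × 28 = 14 entries, which weeks 1 and 2 alone supply, leaving none needed in week 4.
- Treatment, assessed weekly: 0.50 × 7 = 3.5, so 4 of 7, the same as the SAP scoring threshold.
- Four pain days entered and three pain-free days blank pass either check (4/7 = 57%). The checks therefore do not remove the error in step 2.

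**The case against.** The strongest reply is that the daily rule is already clear. Explanation 1 asks for an entry every day with no blanks. Protocol 8.2.2 requires daily completion and training, and the VAS has a 0 for no pain. Diaries are brought back and reviewed at visits planned three times a week. Patients must reach 85% completion at baseline. The Filling Explanation may be meant only to limit recall delay, and patients see a Chinese version that the documents do not reproduce.

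Most of this stands, and it lowers the likely number of blanks. It does not remove the contradiction. The 85% check also gives limited reassurance: a patient in pain nearly every day at baseline passes it under either instruction.

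Several stronger readings are tempting but unsupported:
- *The card tells patients to complete it only on pain days.* It does not; its more detailed instruction says the opposite.
- *The SAP rules that a blank pain-free day is missing.* Its text sets the week, not the day, to missing below 4 reports; exclusion of unreported days from the mean is an inference.
- *The error is several times the planned effect.* Pain of 4 on four days gives a true mean of 16/7 = 2.29 against an analysed 4.0, an error of 1.71. That is one hypothetical patient's error and cannot be set against a 0.5 difference between arm means.
- *The best responders are imputed from worse patients.* The SAP specifies no imputation model, and earlier diary weeks could be among the predictors.
- *The compliance rule leaves week 4 unprotected.* This holds only under the four-weekly wording, not under Protocol 7.3.

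**Conclusion.** The point holds as an internal contradiction on the form that supplies the primary endpoint, together with a missing SAP rule for blank days. A patient who follows a printed instruction could produce a week-4 mean that is too high by about 0.3 to 2 points, or a week that is imputed. This assumes that all pain-free days are blank, that pain-day levels are 2 to 5, and that unreported days drop out of the mean. The 85% baseline requirement means that any distortion would fall mainly on the post-treatment value.

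A true effect on the primary and responder endpoints could be attenuated. Neither the size nor the certain direction of the between-arm bias follows from the documents: no frequency of blanks or of pain-free days is given, and error common to both arms cancels. A reader might infer that the trial's effect estimate will be biased towards no difference; the documents support only that it could be. The correction is worth making because the error is outcome-dependent and cheap to prevent.

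**What to change.** 1. **Card.** Replace the sentence in the Filling Explanation with wording that agrees with Explanation 1, for example: *Complete one entry every day at 19:00, including days without pain; write 0 if you had no pain in the last 24 hours.* Optionally add a tick box for no pain (0). Make the same change in the Chinese card.
2. **SAP 8.2.** State how a blank day is classified. Alongside the planned multiple imputation, add a sensitivity analysis that scores blank days as 0 for participants still in follow-up, for the week-4 change and both responder endpoints. It is a bounding analysis, since some blanks will be forgotten days with pain. It remains useful if cards are already in use.
3. **Compliance.** Reconcile the weekly check in Protocol 7.3 (50%, in practice 4 of 7 entries) with the four-weekly check in Protocol 8.2.2 and SAP 6.4. A weekly check would ensure entries in week 4, but does not substitute for items 1 and 2.

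The cost is a revised card, a few sentences of text and one extra sensitivity analysis. The sample size is unaffected.
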